**Serious adverse events by SOC and PT ([no. of events] no. of patients (pct of patients) )**

| System Organ Class                                   | Preferred term      | etoricoxib N=13 | H56:IC31 TB vaccine N=12 | Control N=12 | etoricoxib and H56:IC31 TB vaccine N=10 |
|------------------------------------------------------|---------------------|-----------------|--------------------------|--------------|-----------------------------------------|
| General disorders and administration site conditions | Disease progression | [1] 1 (7.7%)    |                          |              |                                         |
| Nervous system disorders                             | Cerebral ischaemia  |                 |                          | [1] 1 (8.3%) |                                         |
| Respiratory, thoracic and mediastinal disorders      | Haemoptysis         |                 |                          | [1] 1 (8.3%) |                                         |
| Skin and subcutaneous tissue disorders               | Rash                | [1] 1 (7.7%)    |                          |              |                                         |
|                                                      | Rash generalised    |                 |                          |              | [1] 1 (10.0%)                           |

**Suspected unexpected adverse reactions by SOC and PT ([no. of events] no. of patients (pct of patients) )**

| System Organ Class                     | Preferred term | etoricoxib N=13 | H56:IC31 TB vaccine N=12 | Control N=12 | etoricoxib and H56:IC31 TB vaccine N=10 |
|----------------------------------------|----------------|-----------------|--------------------------|--------------|-----------------------------------------|
| Skin and subcutaneous tissue disorders | Rash           | [1] 1 (7.7%)    |                          |              |                                         |

**Adverse events leading to study drug discontinuation by SOC and PT ([no. of events] no. of patients (pct of patients) )**

| System Organ Class                                   | Preferred term           | etoricoxib N=13 | H56:IC31 TB vaccine N=12 | Control N=12 | etoricoxib and H56:IC31 TB vaccine N=10 |
|------------------------------------------------------|--------------------------|-----------------|--------------------------|--------------|-----------------------------------------|
| Gastrointestinal disorders                           | Abdominal pain upper     | [1] 1 (7.7%)    |                          |              |                                         |
|                                                      | Gastritis                | [1] 1 (7.7%)    |                          |              |                                         |
|                                                      | Nausea                   | [1] 1 (7.7%)    |                          |              |                                         |
|                                                      | Vomiting                 |                 |                          |              | [1] 1 (10.0%)                           |
| General disorders and administration site conditions | Fatigue                  | [1] 1 (7.7%)    |                          |              |                                         |
| Investigations                                       | Hepatic enzyme increased | [3] 2 (15.4%)   |                          |              |                                         |
| Nervous system disorders                             | Dizziness                |                 |                          |              | [1] 1 (10.0%)                           |
| Skin and subcutaneous tissue disorders               | Hyperhidrosis            |                 |                          |              | [1] 1 (10.0%)                           |

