We calculated the numbers and proportions of participants in the SAS that experienced an AE, SAE, and SUSAR by study arm and above defined three time intervals. We also calculated the number and proportions of participants with 1, 2, or  $\geq 3$  AEs, SAEs, and SUSARs; the number and proportion of participants with any treatment related AE and SAE; and, the number and proportion of participants with an AE/SAE leading to study drug discontinuation in each study arm and above defined three time intervals. No formal statistical testing of differences between the study arms was performed. Further, we described the total number of AEs, SAEs, SUSARs, treatment related AEs and SAEs, and AEs/SAEs leading to study drug discontinuation independent of number of participants. In addition, we described the absolute, number of participants with and proportion of participants with AE, SAE, SUSAR, severe AEs, and AEs leading to study drug discontinuation by system organ class (SOC) and preferred term (PT), without calculating any p-values.

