**Supplementary Table 9. Adverse events (AE) tables Day 0 to day 84. Safety Analysis Set\* (N=47)**

**Summary of AEs**

|                                                    | etoricoxib N=13 | H56:IC31 TB vaccine N=12 | Control N=12 | etoricoxib and H56:IC31 TB vaccine N=10 |
|----------------------------------------------------|-----------------|--------------------------|--------------|-----------------------------------------|
| Any AE                                             | 11 (84.6%)      | 11 (91.7%)               | 11 (91.7%)   | 9 (90.0%)                               |
| Number of AEs                                      | 58              | 45                       | 54           | 52                                      |
| Number of SAEs                                     | 2               | 0                        | 2            | 1                                       |
| Number of SUSARs                                   | 1               |                          |              |                                         |
| One AE                                             | 1 (7.7%)        | 4 (33.3%)                | 1 (8.3%)     | 1 (10.0%)                               |
| Two AEs                                            | 1 (7.7%)        | 2 (16.7%)                |              |                                         |
| Three or more AEs                                  | 9 (69.2%)       | 5 (41.7%)                | 10 (83.3%)   | 8 (80.0%)                               |
| Any SAE                                            | 2 (15.4%)       |                          | 1 (8.3%)     | 1 (10.0%)                               |
| Any SUSAR                                          | 1 (7.7%)        |                          |              |                                         |
| Any treatment related AE                           | 10 (76.9%)      | 0                        | 0            | 9 (90.0%)                               |
| Any treatment related SAE                          | 2 (15.4%)       |                          |              | 1 (10.0%)                               |
| Any AE leading to study drug discontinuation       | 2 (15.4%)       |                          | 1 (8.3%)     | 4 (40.0%)                               |
| Number of AE leading to study drug discontinuation | 2               |                          | 1            | 7                                       |

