**AE by System Organ Class (SOC) and Preferred term (PT) ([no. of events] no of patients (% of patients))**

| System Organ Class                                   | Preferred term                              | etoricoxib N=13 | H56:IC31 TB vaccine N=12 | Control N=12  | etoricoxib and H56:IC31 TB vaccine N=10 |
|------------------------------------------------------|---------------------------------------------|-----------------|--------------------------|---------------|-----------------------------------------|
| Blood and lymphatic system disorders                 | Anaemia                                     |                 |                          | [1] 1 (8.3%)  |                                         |
|                                                      | Leukopenia                                  |                 |                          |               | [1] 1 (10.0%)                           |
|                                                      | Lymphadenopathy                             |                 |                          | [1] 1 (8.3%)  |                                         |
|                                                      | Thrombocytopenia                            |                 |                          |               | [1] 1 (10.0%)                           |
| Gastrointestinal disorders                           | Abdominal discomfort                        | [1] 1 (7.7%)    |                          |               | [1] 1 (10.0%)                           |
|                                                      | Abdominal pain                              | [1] 1 (7.7%)    |                          |               | [2] 2 (20.0%)                           |
|                                                      | Abdominal pain upper                        | [1] 1 (7.7%)    | [1] 1 (8.3%)             | [2] 2 (16.7%) |                                         |
|                                                      | Diarrhoea                                   | [1] 1 (7.7%)    |                          |               |                                         |
|                                                      | Dry mouth                                   | [1] 1 (7.7%)    | [1] 1 (8.3%)             |               |                                         |

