|                                                 | Haemoptysis                     |               |               | [1] 1 (8.3%)  |               |
| Skin and subcutaneous tissue disorders          | Dermatitis acneiform            |               | [1] 1 (8.3%)  | [1] 1 (8.3%)  |               |
|                                                 | Eczema                          |               |               | [2] 2 (16.7%) |               |
|                                                 | Hand dermatitis                 |               |               |               | [1] 1 (10.0%) |
|                                                 | Hyperhidrosis                   |               | [1] 1 (8.3%)  |               | [1] 1 (10.0%) |
|                                                 | Night sweats                    | [1] 1 (7.7%)  |               | [2] 2 (16.7%) | [1] 1 (10.0%) |
|                                                 | Pruritus                        | [2] 2 (15.4%) | [1] 1 (8.3%)  | [2] 2 (16.7%) | [4] 3 (30.0%) |
|                                                 | Pruritus generalised            |               | [1] 1 (8.3%)  |               |               |
|                                                 | Rash                            | [1] 1 (7.7%)  | [1] 1 (8.3%)  | [3] 3 (25.0%) | [1] 1 (10.0%) |
|                                                 | Rash generalised                |               |               |               | [1] 1 (10.0%) |
|                                                 | Urticaria                       | [1] 1 (7.7%)  |               |               |               |
| Vascular disorders                              | Diastolic hypertension          |               | [1] 1 (8.3%)  |               |               |
|                                                 | Haematoma                       |               |               |               | [1] 1 (10.0%) |

**Severe adverse events by System Organ Class (SOC) and Preferred term (PT ([no. of events] no. of patients (pct of patients) )**

| System Organ Class                                   | Preferred term       | etoricoxib N=13 | H56:IC31 TB vaccine N=12 | Control N=12 | etoricoxib and H56:IC31 TB vaccine N=10 |
|------------------------------------------------------|----------------------|-----------------|--------------------------|--------------|-----------------------------------------|

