**Time-line (anti-TB chemotherapy, day 0-182)**

### Supplementary Figure 9

The safety profile of COX2i or H56:IC31 has not yet been determined in a population undergoing treatment for pulmonary TB. Therefore, we will enrol participants in two groups separated by a safety review. Group A includes volunteers for arm #1, arm #2 and arm #3 (2:2:1 randomization). First at the completion of Study Day 98 for all group A participants, the “clinical investigational group” (sponsor, PI, collaborators including representative from the H56:IC31 vaccine manufacturer) will meet and evaluate the cumulative safety data to determine if the observed safety profile meets the criteria to proceed to inclusion of volunteers for group B; arm #4 and remaining Arm #3 controls (2:1 randomization).

Arm #1 (n=10): etoricoxib treatment started at day 0 and given for 20 weeks (day 0-140) followed by 6 weeks (or according to clinical evaluation) of standard anti-TB chemotherapy alone (day 0-182) and follow-up control at day 210 and day 238.

Arm #2 (n=10): given anti-TB chemotherapy alone (day 0-182) (or according to clinical evaluation) and follow-up control at day 210 and day 238. TB vaccine H56:IC31 will be injected at day 84 and day 140.

Arm #3 (controls, n=10): given anti-TB chemotherapy alone (day 0-182) (or according to clinical evaluation) and follow-up control at day 210 and day 238.

Arm #4 (n=10): etoricoxib treatment started at day 0 and given for 20 weeks (day 0-140) followed by 6 weeks (or according to clinical evaluation) of standard anti-TB chemotherapy alone and follow-up control at day 210 and day 238. TB vaccine H56:IC31 will be injected at day 84 and day 140.

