### 5.1.3 Description of placebo

No placebo for etoricoxib or H56:IC31 will be used.

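### Supplementary Table 9 (day 0 to 84) gives two incompatible counts of adverse events leading to study drug discontinuation: 2/blank/1/7 by arm in the summary, 7/0/0/3 in the itemised list

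*Protocol*

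**What the plan says.** The section on the primary safety endpoint lists, among its outputs, the number and proportion of "participants with an AE/SAE leading to study drug discontinuation in each study arm" for each of three time intervals, together with the total number of such events.

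Supplementary Table 9 reports this for day 0 to 84, in the safety analysis set, with 13, 12, 12 and 10 patients in the etoricoxib, H56:IC31, control and combination arms. It does so in two places:

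- **Summary of AEs.** The event row begins "Number of AE leading to study drug discontinuation | 2" and continues blank, 1, 7. The patient row, "Any AE leading to study drug discontinuation", reads 2 (15.4%), blank, 1 (8.3%), 4 (40.0%).
- **List by system organ class and preferred term.** Each cell shows events in brackets, then patients and a percentage. The etoricoxib arm has one event each of abdominal pain upper, gastritis, nausea and fatigue, and the entry "Hepatic enzyme increased | [3] 2 (15.4"%). The combination arm has one event each of vomiting, dizziness and hyperhidrosis. The other two arms are empty.

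On the control arm, Section 3 says: "Arm #3 (controls, n=10): given anti-TB chemotherapy alone (day 0-182"). Section 5.1.3 says: "No placebo for etoricoxib or H56:IC31 will be used". Section 5 names only Arcoxia and H56:IC31 as investigational products.

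**The concern.** Two outputs with the same label, interval, analysis set and arm sizes should give the same totals. These do not, so at least one set of printed counts is wrong.

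The item matters because the primary objective (Section 2) is the safety and tolerability of etoricoxib alone and in combination with the vaccine, and stopping study drug for an adverse event is a direct measure of tolerability. No formal test between arms was done, so a reader has only these counts to go on. By events, the summary makes the combination look worse tolerated, and the list makes etoricoxib alone look worse tolerated.

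**Working it through.** **1. Event totals.** The bracketed counts in the list were summed by arm and compared with the summary row.

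| | Etoricoxib (13) | H56:IC31 (12) | Control (12) | Combination (10) | Total |
|---|---|---|---|---|---|
| Summary | 2 | blank | 1 | 7 | 10 |
| List | 1+1+1+1+3 = 7 | 0 | 0 | 1+1+1 = 3 | 10 |

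The grand totals agree, but three of the four arms differ.

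**2. Patients.** The list does not give patients per arm, but it bounds them. The minimum is the largest patient count for any one term, and the maximum is the sum over terms.

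- Etoricoxib: 2 to 1+1+1+1+2 = 6. The summary's 2 is possible.
- Control: 0. The summary's 1 is impossible.
- Combination: 1 to 1+1+1 = 3. The summary's 4 is impossible.

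**3. Size of the difference, etoricoxib against combination.**

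- Events per patient, summary: 2/13 = 0.15 against 7/10 = 0.70.
- Events per patient, list: 7/13 = 0.54 against 3/10 = 0.30. The direction reverses.
- Patients, summary: 2/13 (15.4%) against 4/10 (40.0%).
- Patients, list: 2 to 6 of 13 (15.4% to 46.2%) against 1 to 3 of 10 (10% to 30%). The direction is open.

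**4. Are the summary and the detailed tables meant to agree?** Yes. Summing events over the full table of adverse events by preferred term gives 58, 45, 54 and 52, which are exactly the numbers of AEs in the summary. The serious adverse event list sums to 2, 0, 2 and 1, again exactly the summary row. The single SUSAR agrees as well. Among these rows only the discontinuation rows fail.

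**5. Other explanations.**

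- *Columns shifted when the table was read.* Every percentage fits its own column: 1/13 = 7.7%, 2/13 = 15.4%, 1/12 = 8.3%, 1/10 = 10.0%, 4/10 = 40.0%. Four patients of 13 would be 30.8%.
- *One output uses a wider definition.* The summary is below the list for etoricoxib (2 against 7) but above it for control (1 against 0) and combination (7 against 3). No single wider or narrower definition does that.
- *The two etoricoxib-containing arms are swapped in the list.* In the full adverse event table, "Abdominal pain upper" and gastritis have no event in the combination arm, while "Hyperhidrosis" and vomiting have none in the etoricoxib arm. The list entries are therefore in the only arms where they can be.
- *The two cells are swapped in the summary.* The row would read 7, blank, 1, 2. Etoricoxib would match, but control (1 against 0) and combination (2 against 3) would not.
- *Re-categorisation.* The footnote on recoding an interruption as a discontinuation stands under Supplementary Table 10 and concerns day 85 to 154 only.

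**The case against.** The arithmetic is not in dispute. The best case on the other side concerns what it amounts to.

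- **These are reported results, not planned methods.** This is true. The planned output is not at fault; its tabulation is. The point is a reporting error in a named primary safety output, and it asks for no change of method.
- **Events are the weaker measure.** One patient can contribute several events to a single stop, so patients are the better unit for tolerability, and there the reversal is unproven. This stands, and the conclusion is limited accordingly. The patient counts still conflict outright in two arms (control and combination).
- **Two overlapping definitions could be in play**, such as withdrawal from the study in one output and permanent drug stop in the other. Supplementary Table 8 gives some support: over the whole study the etoricoxib arm has one withdrawal for safety and one for TB progression, and the control arm has one for autoimmune disease or immunosuppressive therapy. That resembles the summary's 2 and 1. However, the combination arm there has two safety withdrawals, one pregnancy and one move abroad, which does not clearly explain 4 patients with 7 events. Even if this is the cause, one output carries the wrong label.
- **The consequence is limited.** The arms have 10 to 13 patients, nothing was tested, and nothing in the document shows a decision resting on either row. That argues for a modest grading, not for leaving the contradiction in place.

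**Conclusion.** The two outputs cannot both be right. They differ in three of four arms for events (2 against 7, 1 against 0, 7 against 3), and in the control and combination arms the summary's patient counts are impossible under the list. The events-per-patient comparison of etoricoxib alone with the combination changes direction, from 0.15 against 0.70 to 0.54 against 0.30; whether the patient comparison does so is unknown.

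The control entry is wrong as labelled on any reading, because that arm had no study drug to discontinue. Beyond that, the document does not show which output is in error, and both may be.

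The conclusion assumes only that both outputs are meant to report the same thing, which their shared label and the exact agreement of the other rows support. The error should be corrected, but it does not touch the design or the other adverse event totals.

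**What to change.** 1. Re-derive adverse events leading to study drug discontinuation for day 0 to 84, by arm, for both events and patients. Use the action taken in the eCRF, last-dose dates, drug accountability logs and reasons for withdrawal.
2. Make the summary and the list in Supplementary Table 9 agree. Set the control arm to none or not applicable. If the control entry proves to be a withdrawal from the study, report it under that heading.
3. While doing this, check three serious adverse events that are absent from the list: disease progression and rash in the etoricoxib arm, and the generalised rash, also graded severe, in the combination arm. The summary's counts of patients with treatment-related serious events (2 and 1) equal its counts of patients with any serious event in those arms, so all of these patients had a related one. Sections 5.3, 6.3.2 and 6.4.1 make a drug stop plausible, but the document does not settle whether one occurred.
4. In the summary of Supplementary Table 10, relabel the discontinuation row. It is headed as a number of events but shows 1 (9.1%) for H56:IC31, which is 1/11 patients. That fits one patient with the two events (lymphadenopathy and abdominal pain) in that table's list.

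The cost is minor: one descriptive output re-derived from existing data and one row label, with no new data and no design change.

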**Most frequent AEs (4 or more occurrences) by PT ([no. of events] no. of patients (pct of patients) )**

| Preferred term           | etoricoxib N=13 | H56:IC31 TB vaccine N=12 | Control N=12  | etoricoxib and H56:IC31 TB vaccine N=10 |
|--------------------------|-----------------|--------------------------|---------------|-----------------------------------------|
| Fatigue                  | [9] 8 (61.5%)   | [4] 4 (33.3%)            | [6] 6 (50.0%) | [3] 3 (30.0%)                           |
| Nausea                   | [7] 6 (46.2%)   | [4] 4 (33.3%)            | [3] 3 (25.0%) | [6] 5 (50.0%)                           |
| Arthralgia               | [3] 3 (23.1%)   | [3] 3 (25.0%)            | [6] 6 (50.0%) | [2] 2 (20.0%)                           |
| Headache                 | [6] 6 (46.2%)   | [5] 5 (41.7%)            | [2] 2 (16.7%) | [2] 1 (10.0%)                           |
| Hepatic enzyme increased | [8] 5 (38.5%)   | [3] 3 (25.0%)            | [3] 2 (16.7%) | [4] 3 (30.0%)                           |
| Myalgia                  | [3] 3 (23.1%)   | [4] 2 (16.7%)            | [2] 2 (16.7%) | [2] 2 (20.0%)                           |
| Pruritus                 | [2] 2 (15.4%)   | [1] 1 (8.3%)             | [2] 2 (16.7%) | [4] 3 (30.0%)                           |
| Rash                     | [1] 1 (7.7%)    | [1] 1 (8.3%)             | [3] 3 (25.0%) | [1] 1 (10.0%)                           |
| Dizziness                | [3] 3 (23.1%)   |                          | [1] 1 (8.3%)  | [2] 2 (20.0%)                           |
| Dyspepsia                | [1] 1 (7.7%)    | [3] 2 (16.7%)            | [2] 2 (16.7%) |                                         |
| Decreased appetite       |                 |                          | [4] 4 (33.3%) | [1] 1 (10.0%)                           |
| Cough                    |                 | [1] 1 (8.3%)             | [2] 1 (8.3%)  | [2] 2 (20.0%)                           |
| Night sweats             | [1] 1 (7.7%)    |                          | [2] 2 (16.7%) | [1] 1 (10.0%)                           |
| Chest pain               | [1] 1 (7.7%)    | [3] 3 (25.0%)            |               |                                         |
| Abdominal pain upper     | [1] 1 (7.7%)    | [1] 1 (8.3%)             | [2] 2 (16.7%) |                                         |

